# Community-based heat-sensitive moxibustion for primary hypertension: study protocol for a randomized controlled trial with patient-preference arms

**DOI:** 10.1186/s13063-022-06092-4

**Published:** 2022-02-16

**Keywords:** Heat-sensitive moxibustion, Primary hypertension, Community healthcare, Pragmatic trial

## Abstract

**Background:**

Low- and middle-income countries have a high prevalence of primary hypertension, but its treatment and control are often low. Heat-sensitive moxibustion (HSM), an innovative acupoint stimulation technique, may be effective for treating hypertension and thus used appropriately in primary healthcare. The objective of this study is to investigate whether HSM is effective and safe for the treatment of primary hypertension in the community.

**Methods:**

This study is a multicenter, pragmatic, randomized controlled trial (RCT) with patient-preference arms. Four hundred patients with primary hypertension from seven communities will be enrolled. Initially, the communities will be randomly assigned into two study clusters, one using compulsory randomization and the other allowing treatment selection by patient preferences. Then, patients in the compulsory randomization cluster will be randomized to receive HSM plus their original antihypertensive regimen (HSM group) or only their original antihypertensive regimen (control group) for 6 months. Patients in the patient preference cluster may choose to receive HSM or control if they have a preference; otherwise, patients will be randomly assigned. The primary outcome is the change in systolic blood pressure from baseline; secondary outcomes include change in diastolic blood pressure, dosage of antihypertensive drugs, quality of life (QoL), severity of hypertensive symptoms, and incidence of cardiovascular events. Patient compliance with the HSM regimen, the cost-effectiveness ratio, and safety outcomes will also be evaluated. Outcome data will be collected at 6 monthly visits.

**Discussion:**

This trial will provide important evidence regarding HSM as a technique for primary hypertension in primary healthcare settings. Given the randomization with patient preferences considered, the trial will also allow analyzing patient-preference effects and the comparison of randomized and nonrandomized samples, to improve the robustness and extrapolation of study conclusions.

**Trial registration:**

ClinicalTrials.govNCT04788563. Registered on March 9, 2021.

**Supplementary Information:**

The online version contains supplementary material available at 10.1186/s13063-022-06092-4.

## Background

Hypertension is a major risk factor for cardiovascular disease and premature death and affects approximately one-third of the population worldwide [1]. Low- and middle-income countries have a higher burden of hypertension, resulting in fewer disability-adjusted life years and higher hypertension-related mortality than high-income countries, highlighting the challenge of hypertension management in these countries [1, 2]. In China, for example, one episode of intensive blood pressure control costs up to $766, which in 2015 was equivalent to 22.7% of the average citizen’s annual disposable income [3], while the rate of optimally controlled hypertension has remained low in the past dozen years [4].

A key reason for the imbalance in cost-effectiveness in low- and middle-income countries may be that primary healthcare interventions for hypertension are not yet well developed [5, 6]. Despite consensus on the effects of reducing blood pressure and cardiovascular disease risk with long-term adherence to antihypertensive drugs, under a single hospital management model, a large proportion of patients cannot maintain their blood pressure at the ideal level [7]. Indeed, patients often discontinue their medication because of inconvenience in accessing medical care or concerns about adverse effects. Therefore, developing appropriate treatment regimens for hypertension that are effective, safe, and inexpensive and can be widely popularized in the community is warranted to compensate for the inadequacy of the hospital management model [8].

Moxibustion is an acupoint stimulation therapy that has been employed as a complementary and alternative therapy in Chinese medicine for thousands of years. In moxibustion, burning moxa sticks are used to stimulate specific acupoints with heat. Specifically, when patients receive moxibustion therapy, they may be stimulated with “heat-sensitized sensations”, as follows: heat penetration, in which the patient can feel the moxa heat penetrating through the skin into deep tissues (the skin surface may or may not be hot); heat diffusion, in which the patient can feel the moxa heat spreading to the surrounding area (the vicinity of the acupoint may or may not be hot); heat conduction, in which the patient can feel the moxa heat transferring a distance in one direction; and nonthermal sensation, in the patient they may feel a creeping sensation, swelling sensation, soreness, coolness, etc. [9]. When patients experience these special sensations, the efficacy of moxibustion can be significantly enhanced compared with conventional moxibustion for multiple diseases, such as osteoarthritis [10], lumbar disc herniation [11], and bronchial asthma [12]. A moxibustion technique with the purpose of stimulating heat-sensitized sensations and applying a saturating moxibustion dose until the sensations disappear is called heat-sensitive moxibustion (HSM).

Overall, HSM has the potential to become an appropriate technique for the management of hypertension in the community because it is simple, convenient, effective, and inexpensive. For example, moxa heat stimulation at acupoints has been demonstrated to induce positive changes in the levels of renin activity, atrial natriuretic peptide, and aldosterone in plasma, resulting in a reduction in blood pressure [13]. HSM is also considered to reduce blood pressure by modulating the expression of the mammalian target of rapamycin and decreasing the level of oxidative stress in the body [14]. A meta-analysis including 18 randomized controlled trials (RCTs) found that moxibustion reduced systolic blood pressure (SBP) by 7.85 mmHg and diastolic blood pressure (DBP) by 4.09 mmHg in patients with primary hypertension over a median 4-month course, although it should be noted that the evidence was not for HSM specifically and the quality of evidence was affected by the risk of bias [15]. The HSM technique is also easy to learn and perform; after receiving a short training session, patients can administer moxibustion at home, by themselves or with the help of family members. Moreover, self-administration of HSM becomes more convenient with the use of a moxibustion device (e.g., moxibustion jar).

Nevertheless, implementing HSM for the treatment of hypertension in the community still requires evidence regarding the following critical questions: Does RCT evidence support that HSM is effective for hypertension? Can HSM replace some doses of antihypertensive drugs? What are the safety, compliance, and cost-effectiveness of HSM for hypertension in the community setting? To answer these questions, we plan to perform a pragmatic RCT with patient preference consideration. We hypothesize that adding daily HSM self-management to traditional antihypertensive treatment/no treatment will result in better blood pressure control efficacy than the original antihypertensive regimen, with good safety and lower costs. Given the real-world situation that patients in community settings may adapt different antihypertensive regimens, this pragmatic trial will be based on an add-on comparison (i.e., HSM + original antihypertensive regimen vs. original antihypertensive regimen) to validate the hypotheses, which will also facilitate maintaining patients’ original preference in the patient-preference arms and observing changes in dosage of antihypertensive drugs over the study period.

## Methods/design

### Study design

The study protocol has been registered at ClinicalTrials.gov (Identifiers: NCT04788563), a registry including all items from the WHO Trial Registration Data Set. We developed this article following the Standard Protocol Items: Recommendations for Interventional Trials (SPIRIT) guidelines [16].

This study will be a multicenter, pragmatic, parallel-group, superiority RCT with patient-preference arms. We will recruit patients from seven communities (Wuliangdian, Nangang, Jinsheng, Shajing, Hongmiao, Jinghexinggong, and Erliuling) to which the Affiliated Hospital of Jiangxi University of Chinese Medicine provides primary healthcare services. These communities will first be randomized into a compulsory randomization cluster and a patient preference cluster. For the former, a completely random grouping scheme to the moxibustion group (HSM + their original antihypertensive regimen) or the control group (their original antihypertensive regimen alone) will be used for individual patients; in the latter, patients can directly enter the moxibustion or control group based on their preference for managing hypertension, whereas the patients will be randomized if they have no clear preference. This grouping method will result in four randomized arms and two nonrandomized arms (Fig. 1).

**Fig. 1 Fig1:**
[figure not shown]
Flowchart of the study. Abbreviation: HSM, heat-sensitive moxibustion

### Study population

Patients who meet the following inclusion criteria will be eligible for the study: (1) diagnosis of primary hypertension for at least 6 months according to the criteria in the International Society of Hypertension’s 2020 Clinical Practice Guideline for Hypertension [17]; i.e., SBP ≥ 140 mmHg and/or DBP ≥ 90 mmHg as office-based or clinical repeated measurements without antihypertensive medication [17]; (2) age between 18 and 80 years; (3) the use of antihypertensive drugs limited to calcium channel blockers and/or angiotensin II receptor blockers; and (4) no acupoint stimulation therapy (e.g., acupuncture, moxibustion, acupressure, etc.) for treating hypertension within the last month. In addition, patients in the HSM group must be able to stimulate at least one heat-sensitized sensation around any main acupoint.

Patients with the following conditions will not be eligible for participation: (1) SBP ≥ 180 mmHg or DBP ≥ 110 mmHg despite the use of antihypertensive drugs; (2) secondary hypertension caused by acute glomerulonephritis, renal artery stenosis, primary aldosteronism, pheochromocytoma, aortic stenosis, etc.; (3) pregnancy or lactation; (4) allergy to moxa smoke or moxa leaves/velvet; and (5) complications of any disease not compatible with HSM according to the Technical Practice Guideline of Heat-Sensitive Moxibustion [18], such as acute cerebral hemorrhage, hypertensive crisis, sensory impairment, and severe mental illness.

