### Allocation

For randomization, the “blockrand” function in R 4.1.0 (Ross Ihaka, Robert Gentlemen, New Zealand) will be employed to generate random sequences. We will first divide the seven communities into the compulsory randomization cluster (three communities) and patient preference cluster (four communities) via cluster randomization. Then, we will generate a random sequence with a block size of four to randomly assign the patients into the HSM or control group in a 1:1 ratio in a compulsory or voluntary manner.

The random sequence will be concealed using scratch cards printed with a random number corresponding to the participation order. Until the coating is scratched, neither the patients nor the investigators will have knowledge about the group assignments. An independent investigator who is not involved in the implementation and follow-up of this study will generate and save the randomization sequence and prepare scratch cards. Although blinding is impossible for the patients and physicians, the data analysts will not be aware of the treatment allocation.

Patients who have a clear preference may be free to choose to enter the HSM or control group, with an allocation ratio of 1:1. Hence, when either nonrandomized group is full, the remaining patients will have to enter another nonrandomized group.

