### Interventions and cointerventions

In the HSM group, patients will self-administer HSM to treat hypertension. At trial entry, physicians will follow a predetermined standard operating procedure to stimulate the patient for heat-sensitized sensations using round-trip meridian, circling, and sparrow-pecking techniques around any of the acupoints at Yongquan (KI1), Shenque (CV8), and Baihui (GV20) as well as Dazhui (GV14), Quchi (LI11), Hegu (LI4), Taichong (LR3), and Zusanli (ST36). The former three are the main acupoints, and the latter four are the matching acupoints. The patients will select one main acupoint and one matching acupoint with the strongest heat-sensitized sensation as acupoints for HSM self-administration. For bilateral matching acupoints (i.e., Quchi, Zusanli, Hegu, and Taichong), the side with the stronger heat-sensitized sensation will be selected. The administration of HSM at the matching acupoint can be abandoned if all fail to stimulate heat-sensitized sensations.

After acupoint selection, the physicians will explain in detail the technique of HSM to the patients or their families, including how to use the moxibustion jar, ignition, and safety precautions (e.g., preventing burns and smoke evacuation). When dose saturation is achieved (i.e., the heat-sensitized sensations disappear), HSM can be stopped, or the patient can wait until the moxa column has burned completely (approximately 30 min). We will recommend that patients administer HSM once per day at home or at a community healthcare center. Driven by the pragmatic design, we will allow for a lower frequency of HSM when patients are busy, but the procedure must be completed at least two times per week.

Patients in both the HSM and control groups will maintain the use of their original antihypertensive regimen, including antihypertensive drugs or no treatment. The study treatments will last 6 months for all patients. During the trial period, all patients will be prohibited from receiving other acupoint stimulation therapies, such as acupuncture, acupressure, transcutaneous electrical stimulation, or acupoint application therapy. Regular treatment for comorbidities, such as glucose-lowering drugs for patients with diabetes and lipid-lowering drugs for those with dyslipidemia, will be allowed.

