### Sample size estimation

The primary purpose of sample size estimation is to meet the need for statistical power for primary outcome comparison between randomized groups. Based on the results of our previous nonrandomized studies (not yet published) and expert opinion, we assume that the SBP in the HSM group will be on average 5 mmHg lower than that in the control group after 6 months of HSM treatment, with a common standard deviation of 8 mmHg between the groups. With a type I error probability “α” of 0.05 and type II error probability “β” of 0.20 and the allowance of a 20% attrition rate, a minimum of 51 patients in either the randomized HSM or control group is needed, as calculated by the following formula for the superiority design [22]:
$$ N=2\times {\left(\frac{Z_{1-\frac{\alpha }{2}}+{Z}_{1-\beta }}{\upmu_1-{\upmu}_2}\right)}^2\times {s}^2 $$

We ultimately decided to enlarge the total sample size to 400, as a sample of this size can be supported by funding. We administered a small preference survey to 100 patients at the study sites, which showed that the ratio of patients with a preference (a strong willingness to enter the HSM or control group) to those without a preference (accept the randomization) was approximately 6:1. Considering the feasibility of the study and the need for confounder adjustment, we established a sample size for the voluntary randomization group of 40 (20 per group) such that the size of the preference selection (nonrandomized) group would be 240 (120 per group). The remaining 120 patients will be entered into the compulsory randomization group (60 per group). Figure 1 illustrates the sample size scheme for each arm.

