### Statistical analysis

Data analysis of the primary outcome will be based on the full analysis set constructed by the intention-to-treat principle, whereby patients will remain in their original group regardless of contamination. The per-protocol set will also be analyzed by sensitivity analysis for the primary outcome to evaluate whether contamination impacts the direction of the effect. The secondary outcomes will also be compared based on the per-protocol set. The need to impute missing values will be determined by the proportion of and reasons for missing data. If imputation is necessary, appropriate methods, such as the last observation carried forward, “best-worst-case” scenario and multiple imputation regression modeling, will be chosen according to the distribution of the missing values.

Data analysis will be conducted separately for the randomized and nonrandomized groups, and consistency of effect directions between the two sets of analyses will be evaluated. For the randomized groups, repeated-measures analysis of variance will be employed for the continuous variables measured each month; QoL and symptom scale scores will be compared by *t* tests, and categorical variables will be compared by chi-square tests. These analyses will not be adjusted for covariates unless there are factors that are significantly unbalanced at baseline. For nonrandomized groups, we will utilize repeated-measures ANOVA, linear mixed models, and logistic regression models depending on the data distribution; potential confounders will be adjusted for, including age, body mass index (BMI), baseline SBP, duration of hypertension, type of antihypertensive regimen, diabetes, dyslipidemia, smoking, and alcohol consumption. The between-group difference will be measured by the mean differences for continuous outcomes (i.e., changes in SBP, DBP, dosage of antihypertensive drug, QoL, and hypertensive symptom scores) and the risk ratios (RRs) for binary outcomes (i.e., the response to treatment and incidence of new-onset cardiovascular events).

We are also interested in whether there are different blood pressure lowering effects between HSM regimens with different parameters, which will be explored by the following subgroup analyses with prespecified effect directions based on our clinical experience:

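### The sensation requirement binds only the HSM group and can act only after randomisation, and the protocol does not say how a randomised HSM patient who fails it is handled or analysed

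*Protocol article*

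**What the plan says.** Study population (Protocol article) lists four inclusion criteria for all patients and then adds a fifth requirement for one group: "patients in the HSM group must be able to stimulate at least one heat-sensitized sensation around any main acupoint".

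Allocation describes concealment by scratch card: "Until the coating is scratched, neither the patients nor the investigators will have knowledge about the group assignments".

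Interventions and cointerventions places the sensation test inside the description of the HSM group: "At trial entry, physicians will follow a predetermined standard operating procedure to stimulate the patient for heat-sensitized sensations". No such test is described for controls. For the matching acupoints there is a rule on failure: "The administration of HSM at the matching acupoint can be abandoned if all fail to stimulate heat-sensitized sensations". There is no rule for a patient in whom no main acupoint gives a sensation.

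Statistical analysis bases the primary analysis on a "full analysis set constructed by the intention-to-treat principle, whereby patients will remain in their original group regardless of contamination". It uses the per-protocol set for a sensitivity analysis of the primary outcome and for the secondary outcomes. On the randomised comparison it adds: "These analyses will not be adjusted for covariates unless there are factors that are significantly unbalanced at baseline".

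**The concern.** A randomised patient can be identified as belonging to the HSM group only once the card has been opened. A requirement on that group alone is therefore a post-randomisation criterion with no counterpart among controls. The contrast with the rest of the section is telling: allergy to moxa and diseases incompatible with HSM exclude patients from both groups.

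If failing the requirement leads to exclusion, the HSM arm holds only sensation-positive patients while the control arm holds a mixture, and the two are no longer exchangeable. Default adjustment would not repair this, since no sensation status is described for controls. The judgement would also be made unblinded. Under Data collection and management, one community physician per site handles recruitment, HSM training and outcome assessment, and the Allocation section accepts that physicians cannot be blinded.

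The randomised comparison is the trial's main evidence, so the handling of these patients should be fixed before analysis.

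**Working it through.** **Inputs from the protocol (Sample size estimation).** Difference 5 mmHg ("SBP in the HSM group will be on average 5 mmHg lower than that in the control group"), SD 8 mmHg, two-sided α 0.05, power 0.80, attrition 20%. Planned randomised patients per group: 60 compulsory + 20 voluntary = 80.

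**Assumed inputs; the protocol gives neither.**
- q: share of patients with no sensation at any main acupoint, 10–30%.
- g: gap in 6-month SBP change, without HSM, between sensation-positive and sensation-negative patients, 0–5 mmHg in either direction.

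**1. The protocol's own figure.** N = 2 × ((1.96 + 0.84)/5)² × 8² = 40.19 with unrounded normal quantiles. 40.19/0.80 = 50.23, rounded up to 51. The stated minimum is reproduced.

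**2. Shift if response depends on sensation.** Suppose HSM lowers SBP by 5 mmHg in sensation-positive patients and by nothing in the others, and g = 0.
- All randomised patients kept: expected difference = (1 − q) × 5.
- Non-sensitive HSM patients removed: expected difference = 5.

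| q | All kept | Removed |
|---|---|---|
| 10% | 4.5 mmHg | 5 mmHg |
| 20% | 4.0 mmHg | 5 mmHg |
| 30% | 3.5 mmHg | 5 mmHg |

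Removal here changes the population to which the estimate applies. It does not create an effect where there is none.

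**3. Bias if HSM does nothing.** Let m₁ and m₀ be the mean SBP changes of sensation-positive and sensation-negative patients without HSM, so g = m₁ − m₀. After one-sided removal the HSM mean is m₁ and the control mean is (1 − q)m₁ + q·m₀. The difference is q × g.
- g = 0: bias 0 for any q.
- g = 5 in absolute value: 0.1 × 5 = 0.5; 0.2 × 5 = 1.0; 0.3 × 5 = 1.5 mmHg.

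With 64(1− q) HSM patients against 64 controls after 20% attrition, the standard error is 8 × √(1/[64(1 − q)] + 1/64). At g = 5 the two-sided false-positive rate (normal approximation) is about 6%, 10% and 16% for q = 10%, 20% and 30%, instead of 5%. The sign of g is unknown.

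**4. Power for 5 mmHg after removal.** With 80 per group and 20% attrition, 64 per group remain: standard error 8 × √(2/64) = 1.41 and power 94%. With q removed from the HSM arm first, power is 93%, 92% and 89% for q = 10%, 20% and 30%.

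**5. Power if all are kept and the non-sensitive gain nothing.** With 64 per group and differences of 4.5, 4.0 and 3.5 mmHg, power is 89%, 81% and 70%.

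Steps 4 and 5 pool the compulsory and voluntary randomised arms.

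**The case against.** The best defence is that the article nowhere says such patients are withdrawn, excluded or replaced, and that the intention-to-treat rule keeps patients in their original group. On that reading contamination is only an illustration of the principle, and the primary analysis is safe. This stands in part: a reader might infer that non-sensitive HSM patients are removed, but the text does not state it. What remains is a conflict between an eligibility requirement and an analysis rule. The per-protocol set, which carries the secondary outcomes, is not protected by that rule.

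The timing is also inferred. The test takes place at trial entry, which is not explicitly placed before or after scratching, and the flowchart and visit schedule are not available to settle the order. That is a fair limit, but testing everyone earlier would not cure a requirement worded for one group.

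Two further readings are tempting and unsupported. One is that the bias favours HSM even if HSM does nothing. The Background and the planned subgroup analyses link sensation to the response to moxibustion, not to the course of blood pressure without it; under the null that mechanism contributes nothing. The other is that the HSM arm would be too small. The protocol plans 80 per randomised group against 51 needed, and about 92% power remains with 20% of the HSM arm removed.

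**Conclusion.** The concern holds as an unreconciled contradiction in the design. A one-arm eligibility requirement can act only after the concealed assignment is revealed, and its consequence for a patient who fails is not stated. Exclusion would break the symmetry of the randomised comparison.

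The size rests wholly on assumed values of q and g. If sensation governs response only, exclusion moves the estimate towards the effect in sensation-positive patients, for example 5 instead of 4 mmHg at q = 20% with no benefit in the rest. A spurious effect arises only if sensation status also predicts SBP change without HSM. For q of 10–30% and a gap of 0–5 mmHg it is 0–1.5 mmHg, at most 30% of the planned 5 mmHg, and the documents do not fix its direction. Loss of power from removal is minor.

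**What to change.** Reconcile Study population, Interventions and cointerventions, and Statistical analysis by stating that:
- every randomised patient whose card is scratched stays in the full analysis set of the allocated arm, whatever the sensation result;
- failing the sensation test is not by itself a reason for exclusion from the randomised comparison, including its per-protocol version;
- sensation status is recorded and used only in secondary analyses.

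For patients not yet randomised, the alternative is to run the existing test on all consenting candidates before the card is scratched and apply the criterion to both arms.

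What an HSM patient with no sensation at any main acupoint receives is for the sponsor to reconcile; the current text leaves it open.

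**Cost.** The first option is a wording change and, if made before analysis, also covers patients already enrolled. Its price is dilution, which need not be slight: about 4.0 to 3.5 mmHg and 81% to 70% power if an assumed 20–30% are non-sensitive and gain nothing. The second option exposes future controls to a short stimulation procedure. It cannot help those already randomised, and recruitment began in March 2021.
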